### Randomization

The patients will be randomly assigned to one of the three intervention groups (two, four or six sessions per week) by a 1:1:1 allocation ratio. The generation of the allocation sequence will be attended to by a statistician not involved in the trial in any other way. One hundred and forty opaque and sealed envelopes will be generated. After being included in the trial (signed written informed consent and completion of baseline assessment) a person independent of the trial will open one of these envelopes and inform the patient’s municipality which of the three exercise groups the patient is allocated to. In this way, the allocation information is kept secret from the outcome assessor.

### Blinding

The primary investigator collecting the outcomes (outcome assessor) as well as the data analysts will be blinded to allocation. At outcome assessment sessions, the outcome assessor will start by informing the patients that they are not allowed to mention what exercise dosage they have received. The data will be coded in such a way that group allocation is concealed in the dataset, thus blinding the outcome assessors and data analysts to the group allocation. The patients and the physiotherapists instructing in the intervention will not be blinded due to the nature of the intervention; however, the patients will be blinded to the exercise dosages in the other groups, which exercise dosages will be compared in the analysis and which dosage is hypothesized to have the largest effect. Unblinding will only happen in the case where the wellbeing a the patient is at risk. This will be assessed in collaboration with the patient’s physician.

### Data management

Data from the isometric knee-extensor strength assessment are stored on a computer dedicated to the Metitur equipment as well as being recorded in handwriting in a standardized Case Report Form. The self-reported questionnaires (KOOS and OKS) will be filled in by the patients in paper formats, as this is the way these questionnaires are designed to be filled in. All data from the functional (6MWT and SCT) and pain (NRS) assessments will be recorded on a standardized Case Report Form by the outcome assessor.

Data on exercise adherence from the sensors is saved continuously on the built-in SD card. After the intervention period, the sensors are collected and the exercise data are transferred by Bluetooth from the SD card onto a secure server. The device will not contain any personal data.

Following all outcome assessments, data will be entered into the browser-based research database Research Electronic Data Capture (RedCap 7.1.1) by trial personal using blinded double-data entry to ensure data quality. To further ensure the integrity of the data, anonymous ID numbers will be applied and data quality, data range and data values will be checked to minimize typing errors. All original written information and case report forms will be stored in a secure locker and saved for 3 after the completion of the trial at the trial location. All electronic data will be anonymous (patient IDs), coded and saved on a secure server in the Capital Region of Denmark.

### Statistical analysis

#### Analysis outline

Three groups; group 2 = two sessions/week, group 4 = four sessions/week and group 6 = six sessions/week. There is no control group. The primary outcome is the change in isometric knee-extensor strength. Time from baseline to after 12 weeks of exercise is the primary endpoint (Δ_t0-t1_) and time from baseline to just before hospital discharge, and time from baseline to 3 months after surgery are the secondary endpoints (Δ_t0-t2_ and Δ_t0-t3_, respectively). The analysis plans for the primary and secondary analyses are outlined in Table 3.

**Table 3 Tab3:** Analysis outline for primary and secondary analysis

Variable/outcome	Hypothesis	Outcome measure (unit, scale)	Methods of analysis
Descriptive statistics (sample characteristics)		Age, weight, height, side of index knee (continuous and dichotomous)	Summary statistics
Primary analysis			
Primary outcome			
1. Change in *isometric knee-extensor strength* Δ_t0-t1_	Group 2 < Group 4 Group 4 ≈ Group 6	Change in Nm/kg (continuous)	Analysis of variance ANOVA^a^
Secondary analysis			
Secondary outcomes			
2. Change in *isometric knee-extensor strength* Δ_t0-t2_, Δ_t0-t3_	Group 2 < Group 4 Group 4 ≈ Group 6	Change in Nm/kg (continuous)	ANOVA^a^
3. Change in *Knee Osteoarthritis Outcome Score* (KOOS) subscales Δ_t0-t1_, Δ_t0-t3_	Group 2 < Group 4 Group 4 > Group 6	Change in questionnaire subscales (continuous)	ANOVA^a^
4. Change in *Oxford Knee Score* (OKS) Δ_t0-t1_, Δ_t0-t3_	Group 2 < Group 4 Group 4 > Group 6	Change in questionnaire (continuous)	ANOVA^a^
5. Change in *6-Minute Walking Test for distance* (6MWT) Δ_t0-t1_, Δ_t0-t2_, Δ_t0-t3_	Group 2 < Group 4 Group 4 > Group 6	Change in meters walked (continuous)	ANOVA^a^
6. Change in *Stair Climb Test* (SCT) Δ_t0-t1_, Δ_t0-t2_, Δ_t0-t3_	Group 2 < Group 4 Group 4 > Group 6	Change in time used to ascend and descend stairs (continuous)	ANOVA^a^
7. Change in *current knee pain* (Numeric Rank Scale, NRS) Δ_t0-t1_, Δ_t0-t2_, Δ_t0-t3_	Group 2 < Group 4 Group 4 > Group 6	Change in NRS 0–10 (continuous)	ANOVA^a^
8. Change in *knee pain during the last week* (Numeric Rank Scale, NRS) Δ_t0-t1_, Δ_t0-t3_	Group 2 < Group 4 Group 4 > Group 6	Change in NRS 0–10 (continuous)	ANOVA^a^
9 Distribution in *need for surgery*	Group 2 < Group 4 Group 4 > Group 6	Yes, don’t know, no	Summary statistics
Other outcomes			
10. Difference in *adherence to intervention* between groups	Group 2 > Group 4 Group 4 > Group 6 Group 2 > Group 6 We hypothesize differences between groups in adherence (%) to the training intervention (i.e., higher number of sessions per week, the lower adherence (%))	Number of sessions, sets, repetitions and time-under-tension	ANOVA^a^

^a^If data are not normally distributed the non-parametric Kruskal-Wallis test will be used

Analysis of variance: (ANOVA)

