### Trial design

The trial is named the *QUADX-1 trial*. It uses a three-arm, parallel-group, randomized trial design with three intervention groups (exercise dosages) and no control group. No control group is included as the primary purpose of the trial is to investigate the dose-response relationship of the investigated knee-extensor strength exercise dosages. Based on the sample size estimation outlined below, 140 patients will be randomized (1:1:1) to one of three exercise dosages for 12 weeks. Outcomes will be assessed blinded at baseline before the start of the exercise (t_0_), after the exercise intervention, which is before possible surgery (t_1_, primary endpoint), at hospital discharge 1–8 days after surgery (if performed) (t_2_) and, finally, at 3 months after surgery (if performed) (t_3_). A flow chart of the trial is provided below (Fig. 1).

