### Sample size

For a three-group-level One-way ANOVA of a normal mean difference with a two-sided significance level of 0.05, a common standard deviation of 0.22 Nm/kg (isometric knee-extensor strength measurement) [51], and a minimal clinically important difference of 0.15 Nm/kg (15%), a sample size of 126 (42 per group) patients is required to obtain a power of 80%. To allow for a dropout rate of 10%, we will include 140 patients in total for the intention-to-treat (ITT) analysis (3 × 42 + 14 = 140).

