#### Primary analysis

The primary analysis will be between-group contrasts for the primary outcome at the primary endpoint. Figure 6 illustrates a hypothetical presentation of changes in isometric knee-extensor strength at the primary endpoint for the three groups.

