**Fig. 7 Fig7:**
[figure not shown]
A hypothetical presentation of group changes in knee-extensor strength over the whole trial period. NB, control data are from the academic literature [11] and so are the healthy, age-matched, control data (age 66.8 years (6.5 SD)) [7]

For all outcomes (primary and secondary), mean scores with corresponding standard deviations (SD), and between-group contrasts (change scores) with corresponding 95% confidence intervals (95% CI) and *p* value, will be reported at each endpoint (t_0_, t_1_, t_2_ and t_3_) for each group (groups 2, 4 and 6) (Table 4).

**Table 4 Tab4:** Outcomes for primary and secondary analyses

	t_0_ Baseline			t_1_ After 12-week exercise			t_2_ After surgery at hospital discharge			t_3_ 3 months after surgery			Between-group contrasts (change scores) 95% CI (*p*)
Mean, SD	Gp. 2	Gp. 4	Gp. 6	Gp. 2	Gp. 4	Gp. 6	Gp. 2	Gp. 4	Gp. 6	Gp. 2	Gp. 4	Gp. 6	
Isometric knee-extensor strength (Nm/kg)													Primary analysis Δ_t0-t1_ Secondary analysis Δ_t0- t2_, _t0-t3_
6-Minute Walking Test for distance (6MWT)													Secondary analysis Δ_t0-t1_, Δ_t0-t2_, Δ_t0-t3_
Stair Climb Test (SCT)													Secondary analysis Δ_t0-t1_, Δ_t0-t2_, Δ_t0-t3_
Knee Osteoarthritis Outcome Score (KOOS)							Na	Na	Na				Secondary analysis Δ_t0-t1_, Δ_t0-t3_
Oxford Knee Score (OKS)							Na	Na	Na				Secondary analysis Δ_t0-t1_, Δ_t0-t3_
Current knee pain (Numeric Rating Scale (NRS) 0–10)													Secondary analysis Δ_t0-t1_, Δ_t0-t2_, Δ_t0-t3_
Knee pain during the last week (NRS 0–10)							Na	Na	Na				Secondary analysis Δ_t0-t1_, Δ_t0-t3_
Need for surgery now (yes/don’t know/no)	Na	Na	Na				Na	Na	Na	Na	Na	Na	Secondary analysis
Exercise adherence													
• No. sessions (prescribed, completed, % completed)	Na	Na	Na							Na	Na	Na	Secondary analysis
• Seconds of total time-under-tension (TUT) (prescribed, completed, % completed)	Na	Na	Na							Na	Na	Na	Secondary analysis
Adverse events													Secondary analysis

The patients who choose not to be operated with TKA after the exercise period will be followed with annual outcome assessments as part of a small case study.

Descriptive statistics for the trial population will be presented as in Table 5.

**Table 5 Tab5:** Descriptive statistics

	Gp. 2	Gp. 4	Gp. 6	All patients
Age (years)				
Height (cm)				
Weight (kg)				
Gender (m/f)				
Index knee (r/l)				
Kellgren-Lawrence classification (I–IV)				

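### Adjusting the change outcomes for their measured baseline, and dropping the switch to Kruskal-Wallis, would gain precision at almost no cost and always yield the promised contrasts

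*Protocol article*

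**What the plan says.** In the protocol article, Statistical analysis, Analysis outline: "The primary outcome is the change in isometric knee-extensor strength". The method in Table 3 for the primary outcome is "Analysis of variance ANOVA^a", and the same footnoted ANOVA is named for the change outcomes in rows 2 to 8 and for adherence in row 10. The footnote reads "If data are not normally distributed the non-parametric Kruskal-Wallis test will be used". It states no criterion for non-normality. No baseline covariate appears in any analysis; the supplementary models are simple regressions of change on recorded exercise dose.

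On what will be reported, the Primary analysis section says "The primary analysis will be between-group contrasts for the primary outcome at the primary endpoint". The Secondary analyses section commits, for all outcomes, to means with SDs and "between-group contrasts (change scores) with corresponding 95% confidence intervals (95% CI") and a p value.

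On baseline data, the Trial design section says "Outcomes will be assessed blinded at baseline before the start of the exercise", and the Randomization section places allocation after the baseline assessment is complete. The Missing data section plans multiple imputation.

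**The concern.** There are two separate issues.

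First, every randomized patient has a t0 value for every change outcome, yet the model contains arm only. Subtracting the baseline removes its influence fully only when the regression slope of follow-up on baseline is 1. Otherwise baseline-related variance stays in the error term, and a chance baseline difference between arms passes into the observed contrast through regression to the mean. What is at stake is precision that the trial has already paid for.

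Second, if the footnote is triggered, the named test no longer produces what the protocol promises. Kruskal-Wallis returns one omnibus p value on ranks. It gives no difference in Nm/kg, no 95% CI, and nothing that speaks to the 0.15 Nm/kg difference used to size the trial. It also supplies no estimate and standard error to pool by Rubin's rules over the planned imputations.

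**Working it through.** **Inputs from the Sample size section:** three groups, "with a two-sided significance level of 0.05", "a common standard deviation of 0.22 Nm/kg (isometric knee-extensor strength measurement"), difference 0.15 Nm/kg, 42 per group (126), 80% power, 140 after 10% dropout.

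**Assumptions, not in the document:** the correlation rho between t0 and t1 strength (range 0.3 to 0.95 shown); equal variances at t0 and t1; and whether 0.22 is the SD of a change or of a single measurement, which the text leaves open. Both readings are shown.

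**Step 1, the plan's own figure.** One-way ANOVA, noncentral F, with noncentrality lambda = n × Σ(mean − grand mean)² / SD². With means 0, 0.075, 0.15: Σ = 0.075² + 0 + 0.075² = 0.01125, so lambda = 42 × 0.01125 / 0.0484 = 9.76. On 2 and 123 degrees of freedom, power is 79.5%. Exactly 80% needs 43 per group (129). The dropout step is 126 / 0.9 = 140. The stated figures are reproduced closely.

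**Step 2, variance ratio.** Let s be the SD at each time. Var(change) = 2s²(1 − rho). ANCOVA residual variance = s²(1 − rho²). The ratio is (1 − rho²) / [2(1 − rho)] = (1 + rho)/2, which is below 1 for any rho below 1. Variance falls by 25% at rho 0.5, 15% at 0.7, 10% at 0.8 and 5% at 0.9.

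**Step 3, power at 42 per group, means 0, 0.075, 0.15.** ANCOVA uses 122 error degrees of freedom. If 0.22 is the SD of change, the ANCOVA SD is 0.22 × √((1+rho)/2). If 0.22 is the SD of a single measurement, the change SD is 0.22 × √(2(1−rho)) and the ANCOVA SD is 0.22 × √(1−rho²).

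| rho | 0.22 = SD of change: ANOVA → ANCOVA | 0.22 = single-measurement SD: ANOVA → ANCOVA |
|---|---|---|
| 0.3 | 79.5% → 93.9% | 64.2% → 83.4% |
| 0.5 | 79.5% → 90.1% | 79.5% → 90.1% |
| 0.7 | 79.5% → 85.9% | 95.5% → 97.9% |
| 0.8 | 79.5% → 83.8% | 99.5% → 99.8% |
| 0.9 | 79.5% → 81.6% | about 100% for both |
| 0.95 | 79.5% → 80.6% | about 100% for both |

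**Step 4, the hypothesised pattern.** Table 3 expects group 2 below group 4, and group 4 about equal to group 6. With means 0, 0.15, 0.15: Σ = 0.10² + 0.05² + 0.05² = 0.015, so lambda = 42 × 0.015 / 0.0484 = 13.02 and ANOVA already has 90.1% power. Taking 0.22 as the SD of change, ANCOVA gives 94.3% at rho 0.7 and 91.6% at rho 0.9.

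**Step 5, Kruskal-Wallis.** In a simulation of 4,000 trials with 42 per group, equally spaced means and SD 0.22, type I error was 4.2% with normal data and 4.8% with moderately skewed (gamma, shape 4) data. Power against ANOVA was 77.1% versus 79.6% with normal data and 84.4% versus 78.6% with skewed data. The test is sound. What it lacks is an estimate on the outcome scale.

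**The case against.** The strongest reply is that nothing here is broken. ANOVA on change is unbiased under 1:1:1 randomization, matches the declared outcome and is the test that was sized. Chance imbalance adds variance over repeated randomizations, not bias. All of this stands. A reader might infer that the primary analysis is biased or that the sample size fails; the protocol supports neither.

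The size of the gain is also open to challenge, and this stands too. It depends on rho, on the reading of 0.22 and on the pattern of means. The only reliability figures in the protocol (0.98–1.00 between trials, 0.92–0.99 between evaluators) are not 12-week correlations, but they give no reason to leave out high values of rho, where the gain is 1 to 2 points at most.

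On the footnote, one can answer that it replaces a test while the promise of contrasts with 95% CI remains, so the estimate is not withdrawn. That is a fair reading: it would go too far to say that the primary estimate will be lost. But the protocol then does not say how the contrasts would be obtained, or how they would relate to a p value from ranks. A reader might also infer that Kruskal-Wallis cannot be combined with multiple imputation. That is too strong: its statistic is asymptotically chi-square, and rules for combining such statistics over imputations exist. What is missing is an estimate for Rubin's rules.

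Finally, ANCOVA cannot be applied to every row that carries the footnote. Table 4 marks adherence as not applicable at t0, so row 10 has no baseline to adjust for.

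**Conclusion.** The point holds as a low-cost improvement with one internal mismatch. With equal variances at both times, ANCOVA is more precise than the planned analysis for any rho below 1. With unequal variances it is, in large samples, never less precise. The power gain at 42 per group with equally spaced means runs from about 14 points (rho 0.3, 0.22 as SD of change) or 19 points (rho 0.3, 0.22 as single-measurement SD) down to about 1 point or nothing at high rho. No single figure in that range can be singled out, because the protocol fixes neither rho nor the meaning of 0.22.

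The mismatch does not depend on rho: the fallback test cannot itself deliver the between-group contrasts with 95% CI that the protocol defines as its primary analysis and promises for all outcomes. The t2 and t3 outcomes are measured only in operated patients, and ANCOVA does not resolve that selection.

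**What to change.** In Table 3, rows 1 to 8, replace ANOVA by ANCOVA: the outcome (or its change) on arm plus that outcome's own t0 value. Report adjusted between-group contrasts with 95% CI, pooled over the imputations by Rubin's rules. Keep this as the estimate whatever the distribution looks like. In place of the switch to Kruskal-Wallis for these rows, name robust or bootstrap intervals, or a rank test, as a sensitivity analysis only. Leave row 9 (summary statistics) and row 10 (adherence, ANOVA with its existing fallback) as they are.

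The cost is one error degree of freedom per model and a change of analysis wording. No new data or patients are needed. The change should be dated and made before the data are unblinded.

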#### Secondary outcomes

Change in performance-based function (walking distance in 6 min and climbing of stairs), current knee pain and during the last week (numerical rating scale), self-reported disability (Knee Osteoarthritis Outcome Score and Oxford Knee Score) as recommended by Osteoarthritis Research Society International [33, 34], need for surgery and exercise adherence (sessions, sets, reps, TUT).

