##### Surgical status – Need for surgery?

At the second outcome assessment (after the 12-week exercise period (t_1_)) the patients are asked by the outcome assessor “*based on your knee symptoms in the last week would you say that you need knee surgery?*” The outcome assessor is a physiotherapist with insight to the knee OA condition. The answer will be categorized into one of three options: (1) “*yes*” *I believe I need surgery*, (2) *I do not know* or (3) “*no*” *I do not believe I need surgery*.

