#### Secondary analyses

The secondary analyses will be between-group contrasts for the secondary outcomes at the primary and secondary endpoints. Figure 7 illustrates a hypothetical presentation of changes in isometric knee-extensor strength for the three groups during the whole trial period.

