#### Supplementary analyses

The supplementary analyses will be simple regression models in which the three exercise dosage groups will be pooled, allowing us to utilize the full dataset; that is, the exercise dosage recorded by the sensors will be used in the analysis, not the prescribed exercise dosage. The dependent variables will be the change in primary and secondary outcomes from baseline to the primary endpoint and to the secondary endpoints. The independent variable will be exercise dosage, quantified in two ways: (1) as total TUT and (2) as number of completed exercise sessions for each patient (Table 6). Figure 8 illustrates a hypothetical simple regression model with the change in isometric knee-extensor strength (Nm/kg) at the primary endpoint and TUT.

**Table 6 Tab6:** Regression models for supplementary analysis

Supplementary analyses (primary outcome at primary endpoint)		
	Dependent variable (y)	Independent variable (x)
Linear regression model	Change in *isometric knee-extensor strength* Δ_t0-t1_	Exercise adherence Seconds of total time-under-tension (TUT) Number of completed exercise sessions
Supplementary analyses (secondary outcomes at primary and secondary endpoints)		
Linear regression models	Change in *isometric knee-extensor strength* Δ_t0-t2_, Δ_t0-t3_	Exercise adherence Seconds of total time-under-tension (TUT) Number of completed exercise sessions
	Change in *6-minute walk test for distance* (6MWT) Δ_t0-t1, t0-t2, t0-t3_	
	Change in *stair climb test* (SCT) Δ_t0-t1, t0-t2, t0-t3_	
	Change in *Knee Osteoarthritis Outcome Score* (KOOS) subscales Δ _t0-t1, t0-t3_	
	Change in *Oxford Knee Score* (OKS) Δ _t0-t1, t0-t3_	
	Change in *current knee pain* (Numeric Rating Scale, NRS) Δ _t0-t1, t0-t2, t0-t3_	
	Change in *knee pain during the last week* (Numeric Rating Scale, NRS) Δ _t0-t1, t0-t3_	
	Need for surgery (yes/don’t know/no)	
	Averse events

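### Need for surgery: Table 3 offers only descriptive statistics for a between-dosage hypothesis, the text promises a contrast that cannot be computed, and no workable comparison of the randomised arms is specified

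*Protocol article*

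**What the plan says.** All places are in the Protocol article.

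- **Secondary outcomes** counts the item among the secondary outcomes: "need for surgery and exercise adherence (sessions, sets, reps, TUT".
- **Surgical status – Need for surgery?** has the assessor ask the patient at t1. "The answer will be categorized into one of three options": yes, do not know, no.
- **Analysis outline, Table 3, row 9** reads "9 Distribution in *need for surgery", with hypothesis "Group 2 < Group 4 Group 4 > Group 6" and method "Summary statistics".
- **Secondary analyses** states: "The secondary analyses will be between-group contrasts for the secondary outcomes at the primary and secondary endpoints". Above Table 4 it adds: "For all outcomes (primary and secondary), mean scores with corresponding standard deviations (SD), and between-group contrasts (change scores) with corresponding 95% confidence intervals", together with a p value.
- **Table 4** marks the item as not applicable at t0, t2 and t3, and enters it as a secondary analysis in the column for contrasts of change scores with 95% CI and p value.
- **Supplementary analyses, Table 6** lists it as a dependent variable under linear regression models. There the three groups are pooled and "the exercise dosage recorded by the sensors will be used in the analysis, not the prescribed exercise dosage".

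**The concern.** Nine of the ten numbered rows in Table 3 pair a between-group hypothesis with ANOVA, and a Kruskal-Wallis test if the data are not normal. Row 9 is the exception. It has a hypothesis of the same form, but its method is the one used for the baseline characteristics, which carry no hypothesis. The accompanying text says the opposite, promising an inferential contrast for all outcomes, but of a kind this outcome cannot supply.

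An analyst following the protocol therefore has two incompatible instructions, one descriptive and one not computable. How the outcome is compared, or whether it is, could then be settled after the data are seen. The Background presents coordination of non-surgical and surgical care as part of the rationale, so readers are likely to look at this result.

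**Working it through.** The point rests on the text. The arithmetic only shows how precise a comparison by arm would be.

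**1. Can the promised contrast be computed?** A change score needs a baseline value, and Table 4 has none for this item. A mean with SD needs a numerical scale, and the answer is one of three categories with no scores assigned. The rule above Table 4 therefore fails on both parts.

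**2. Does Table 3 supply a substitute?** Row 9 names summary statistics only. The Kruskal-Wallis footnote is attached to the ANOVA rows, so it does not reach row 9.

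**3. Does Table 6 supply one?** Its predictor is completed dosage, measured as total time under tension or number of sessions. Completed dosage arises after randomisation: a patient with a painful knee may both train less and feel more in need of surgery. It is not a contrast of the arms as randomised, which the Missing data section requires of all analyses. Linear regression also does not suit a three-category response, and the section's text again describes the dependent variables as changes.

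**4. Is the hypothesis direction readable?** Rows 3 to 8 carry the same string as row 9. They include KOOS, where higher is better, and stair-climb time and pain, where lower is better. The signs therefore cannot mean larger or smaller raw values throughout. In row 9 they could refer to the number answering yes or to the better result, and these point in opposite directions.

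**5. Patients per arm.** The Sample size section gives SD 0.22 Nm/kg, difference 0.15 Nm/kg, two-sided alpha 0.05, and 42 per group for 80% power. Taking the extreme means 0.15 apart and the third midway (an assumption), the noncentrality is n Σ(μᵢ − μ̄)²/σ² = 42 × (0.075² + 0 + 0.075²)/0.22² = 42 × 0.01125/0.0484 = 9.76. With 2 and 123 degrees of freedom, power is 79.5%. With 10% dropout, 126/0.90 = 140. The stated figures reproduce, and 42 per arm is used below.

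**6. Precision for need for surgery.** The protocol gives no expected rate, so 30% to 70% answering yes is assumed. The 95% CI half-width for a difference between two arms is 1.96 × √(2p(1 − p)/42):
- p = 0.30 or 0.70: 1.96 × √(0.42/42) = 0.196
- p = 0.50: 1.96 × √(0.50/42) = 0.214

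With 46 per arm and p = 0.50 it is 0.204.

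**7. Pairwise power**, yes against the other answers, 42 per arm, two-sided 0.05, normal approximation with a pooled null variance:
- 50% v 30%: (0.20 − 1.96 × 0.1069)/0.1046 = −0.09, power 46%
- 50% v 20%: (0.30 − 1.96 × 0.1041)/0.0988 = 0.97, power 83%

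Starting from 50%, a difference of about 29 points is needed for 80% power.

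**The case against.** Reporting a single categorical item descriptively is a legitimate choice. The answer is the patient's own opinion, the Limitations section warns that motivation for exercise could bias it, and an orthopaedic surgeon re-assesses the need for operation separately. The trial's stated purpose is knee-extensor strength. The choice of test for one categorical secondary outcome is often left to a statistical analysis plan, and one may exist. All of this stands, and it limits the importance of the point. It does not remove the contradiction, because the protocol itself attaches a hypothesis to the item and promises it a p value.

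Three stronger readings are not supported:

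- A reader might infer from row 9 that the arms are never formally compared and that the pooled regression is the only inference. The Secondary analyses text and Table 4 do commit to between-group contrasts. The fault is that the contrast promised does not fit the outcome.
- A reader might infer that the Table 6 regression is meant to answer row 9. It is labelled supplementary, and nothing says that it tests that hypothesis.
- A reader might note that, with no dosage effect, the four-session arm would have the strictly highest percentage of yes answers in about 29% of trials (42 per arm, 30% to 70% yes), and call this a false-support rate. That presumes a rule of taking the highest percentage as support, which no section states. The figure is simply one third less ties.

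**Conclusion.** The concern holds as an internal inconsistency with a practical consequence. Table 3 is descriptive, the text and Table 4 are inferential, the inferential promise cannot be carried out for this outcome, and the only named model uses non-randomised dosage. No workable comparison of the randomised arms is specified for the row 9 hypothesis, and the direction of that hypothesis is unclear.

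This is a modest point about a secondary outcome that should still be corrected. It does not touch the sample size, the primary analysis or any stated figure. The conclusion follows from the text alone. Only the precision and power figures depend on assumed yes rates, and they show that a formal comparison would reliably detect large differences only.

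**What to change.** Choose one of two coherent repairs.

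**Keep the hypothesis.**
- In Table 3 row 9, name one comparison by randomised arm. For example: percentages per arm, pairwise risk differences in yes with 95% CI, and a Kruskal-Wallis or chi-square test. A proportional-odds model is an alternative if do not know is declared the middle category, which the protocol does not currently say.
- State whether the signs in row 9 refer to fewer yes answers or to a better result.
- In the sentence above Table 4 and in Table 4, exempt the item from means and change scores and point to this comparison.
- In Table 6, replace linear regression for this item with an ordinal or logistic model, label it exploratory, and say that the arm comparison addresses row 9.

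**Or make the outcome descriptive.** Drop the row 9 hypothesis and the p value, exempt the item from the Table 4 rule, and still correct the model in Table 6.

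Either repair is a wording change using data already collected. The first costs one more secondary p value and estimates with wide intervals. The second gives up a formal answer on this outcome.
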